# IMPaCT Back study protocol. Implementation of subgrouping for targeted treatment systems for low back pain patients in primary care: a prospective population-based sequential comparison

**DOI:** 10.1186/1471-2474-11-186

**Published:** 2010-08-20

## Abstract

**Background:**

Prognostic assessment tools to identify subgroups of patients at risk of persistent low back pain who may benefit from targeted treatments have been developed and validated in primary care. The IMPaCT Back study is investigating the effects of introducing and supporting a subgrouping for targeted treatment system in primary care.

**Methods/Design:**

A prospective, population-based, quality improvement study in one Primary Care Trust in England with a before and after design. Phases 1 and 3 collect data on current practice, attitudes and behaviour of health care practitioners, patients' outcomes and health care costs. Phase 2 introduces and supports the subgrouping for targeted treatment system, via a multi-component, quality improvement intervention that includes educational courses and outreach visits led by opinion leaders, audit/feedback, mentoring and organisational support to embed the subgrouping tools within IT and clinical management systems.

We aim to recruit 1000 low back pain patients aged 18 years and over consulting 7 GP practices within one Primary Care Trust in England, UK. The study includes GPs in participating practices and physiotherapists in associated services. The primary objective is to determine the effect of the subgrouping for targeted treatment system on back pain related disability and catastrophising at 2 and 6 months, comparing data from phase 1 with phase 3. Key secondary objectives are to determine the impact on:

a) GPs' and physiotherapists' attitudes and behaviour regarding low back pain;

b) The process of care that patients receive;

c) The cost-effectiveness and sustainability of the new clinical system.

**Discussion:**

This paper details the rationale, design, methods, planned analysis and operational aspects of the IMPaCT Back study. We aim to determine whether the new subgrouping for targeted treatment system is implemented and sustained in primary care, and evaluate its impact on clinical decision-making, patient outcomes and costs.

**Study registration:**

International Standard Randomised Controlled Trial Number Register ISRCTN55174281

## Background

Low back pain (LBP) affects over one third of adults at any one time, and each year approximately 3.5 million people in the UK develop back pain [1]. It is the most common reason for middle-aged people to visit their general practitioner (GP), with approximately 6-9% of adults consulting for this condition each year [2]. Although many back pain patients stop consulting their GP within three months, 60-80% of people still report pain or disability a year later, and up to 40% of those who have taken time off work will have future episodes of work absence [3,4]. The societal cost of work absence attributable to back pain, together with back pain related health care utilisation, constitutes a considerable economic burden. Total back pain related costs in the UK are estimated to form 1-2% of gross national product, [5] with National Health Service (NHS) related costs alone in the region of £251 million per annum [1].

Most patients with back pain are treated in primary care, where an estimated 85% will have 'non-specific' LBP, for which diagnostic labelling is discouraged, and treatment is guided by symptoms and the experience and preferences of individual health care practitioners. In the UK, referral to physiotherapy is a popular management option for GPs, with LBP accounting for more than half of physiotherapists' workload [6]. Whilst the focus of primary care treatment is on minimising pain and disability, previous studies have shown variation in clinical practice [7] and highlighted the gap between current practice and best practice recommendations [6,8-12]. Previous studies have also underlined the challenge practitioners face in applying best practice at an individual patient level, their concerns about the need for specialist advice for those with chronic LBP [13] and their capacity to identify and address psychological obstacles to recovery [14].

Patients with poorer physical function and those with psychological obstacles to recovery such as psychological distress, negative feelings about their back pain and increased fear of activity, are more disabled by their pain and are more likely to have a poor outcome [15]. Despite the plethora of clinical guidelines for the management of back pain and the call to use a biopsychosocial framework [15], a key challenge is the early identification of patients at risk of chronicity and subsequently preventing such chronicity [16]. Addressing these factors in primary care at an early stage before they become entrenched and more difficult to treat could lead to better long-term outcomes.

Improved patient outcomes have been demonstrated in some studies where subgrouping has been used to guide treatment [17,18]. Prognostic assessment tools, in primary care, to identify subgroups of patients at risk of persistent LBP and who may benefit from interventions that target key physical and/or psychological obstacles to recovery have been developed and validated. The STarT Back tool [19] is specifically designed for primary care settings and is a subgrouping tool that classifies patients into three categories for targeted treatment, based on the presence of modifiable risk factors for chronic or recurrent LBP. Three targeted treatments for patients and training programmes for clinicians have been developed. A randomised controlled trial (the STarT Back trial) has tested whether subgrouping for targeted treatment is better than best current care (provided by physiotherapists) of non-targeted treatment [20] addressing the call within recent national guidelines for further investigation of 'matching' or subgrouping LBP patients to different treatments [15].

The IMPaCT Back study (IMplementation study to improve Patient Care through Targeted treatment for Back pain) is a quality improvement study designed to introduce and support a subgrouping for targeted treatment system within primary care practice, and to study the effects on patients, practitioners and health care resource use. Many terms are used to describe the process of quality improvement in clinical practice, such as implementation, knowledge diffusion, transfer and exchange, and innovation diffusion. Implementation research is defined as '*the scientific study of methods to promote the systematic uptake of research findings and other evidence-based practices into routine practice, to improve the quality of health care. It includes the study of influences on healthcare professional and **organisation behaviour' *[21]. In this paper, we use the term quality improvement as in the SQUIRE (Standards for Quality Improvement Reporting Excellence) guidelines [22] in recognition that this is a process that needs a systematic and planned approach but that it is also essentially an applied science, driven by experiential learning so that interventions can be modified in response to feedback.

Unlike targeting the general public through mass media campaigns about LBP [23-25] we are targeting health care practitioners and the health care system within which they work. Several previous studies have attempted to change health care practitioner behaviour for LBP [11,26-31] with mixed results. None have investigated subgrouping for targeted treatment systems based on risk identification or provided comprehensive data on the effect of the quality improvement on practitioners' attitudes and behaviours, clinical processes of care, patients' clinical outcomes and cost-effectiveness.

### Study Aims

Working with one Primary Care Trust (PCT) in England, we will introduce a subgrouping for targeted treatment care system for the assessment and management of LBP patients in primary care and evaluate the effects on health care practitioner attitudes and behaviour, care processes, patients' clinical outcomes through to six months following their primary care consultation and cost-effectiveness. Specific objectives are to:

(i) engage GPs, physiotherapists and PCT managers to deliver the new subgrouping for targeted treatment model of care;

(ii) change GPs' and physiotherapists' LBP-related attitudes and clinical behaviours using the subgrouping for targeted treatment approach;

(iii) improve patients' clinical outcomes at 2 and 6 months follow-up;

(iv) estimate the cost-effectiveness of the subgrouping approach, addressing NHS and societal interests;

(v) provide evidence for the sustainability of this care system.

This publication details the rationale, design, the subgrouping for targeted treatment system, study methods, operational aspects and planned analysis of the IMPaCT Back study.

## Methods

### Study Design

A prospective, population-based, quality improvement study of before and after design, comprising three phases:

Phase 1: assessment of GPs' and physiotherapists' attitudes and behaviours regarding LBP, observation of usual clinical practice and clinical outcomes of patients recruited in a 6 month baseline period;

Phase 2: a multi-component, quality improvement intervention comprising educational courses and outreach visits led by opinion leaders, regular audit/feedback and mentoring support for participating health care practitioners in addition to installation of computerised and paper-based systems to support the subgrouping for targeted treatment care system in practice;

Phase 3: assessment of GPs' and physiotherapists' attitudes and behaviours regarding LBP, observation of clinical practice and clinical outcomes of patients, recruited in a 12 month period following roll-out of the new care system.

The study design is summarised in Figure 1.

**Figure 1 F1:**
[figure not shown]
Summary of IMPaCT Back study design

We considered using a clinical trial design with cluster randomisation at the level of GP practice. However, the physiotherapy service is PCT based rather than GP practice based, which would have been likely to lead to contamination of clusters.

### Setting

Participants will be recruited from up to 7 GP practices and their associated physiotherapy services within one NHS PCT in the county of Cheshire, England, UK. An NHS PCT is a type of NHS Trust, part of the NHS in England, that provides primary and community services or commissions them from other providers, and is involved in commissioning secondary care [32]. There are approximately 152 PCTs in England.

### Ethical review

Favourable ethical opinion was obtained from the Cheshire Local NHS Research Ethics Committee (Study number: 07/H1017/143).

### Independent monitoring

A steering committee with an independent chair and lay representation is monitoring the study's progress.

### Participants

Health care practitioners (GPs and physiotherapists) and patients who consult them with LBP are considered participants in this study.

### Health care practitioners' eligibility criteria

All practising GPs at each participating practice and physiotherapists within the associated physiotherapy services receiving LBP referrals from the participating GP practices are eligible for the study. We will select which GP practices within the PCT to invite in order to ensure a breadth of practice settings (urban/semi-rural/rural) and size (small/medium/large). General practices and physiotherapy services are invited to participate following presentations by the study team at meetings of their practice and physiotherapy staff. Strategies to facilitate participation of general practices and physiotherapy services in the study include continuing professional development activities, receiving guidance and feedback on their practice, and the provision of up to date knowledge, skills and tools to support their management of LBP patients.

### Patients' eligibility criteria

Male and female adults aged 18 years or over, consulting one of the participating GP practices with non-specific LBP (with or without leg pain). Participants must understand English to a level where they can read the study information leaflet and study questionnaires. Exclusions are those with "red flags" (indicative of possible serious spinal pathology such as cauda equina, inflammatory arthritis, malignancy, infection, fracture); pregnancy-related LBP; conditions which might exclude the patient from physiotherapy treatment (e.g. serious co-morbidity, recent major surgery), patients already receiving physiotherapy treatment for this episode of LBP.

The procedures for recruitment, assessment and treatment are summarised below for each phase of the IMPaCT Back study.

### Phase 1: Observation of usual clinical practice and patients' outcomes

We will collect data on health care practitioners' back pain-related attitudes and behaviours, patients' clinical outcomes and health care resource use before the introduction of the new subgrouping for targeted treatment system. Data collection in phase 1 will consist of:

#### a) Health care practitioners' attitudes and behaviour and care processes

Attitudes and reported behaviour: We will conduct a questionnaire survey of participating GPs and physiotherapists to describe their attitudes and beliefs about back pain and its management, and their reported clinical behaviour relating to two clinical case vignettes developed from real patients with LBP. The questionnaire and case vignettes have been adapted from a previous national survey of GPs and physiotherapists [7]. The self-report questionnaire will include key demographic and clinical experience questions, a measure of beliefs and attitudes towards LBP, the Pain Attitudes and Beliefs Scale (PABS) [33,34], and a measure of self-confidence in managing LBP patients [35]. Full details of the contents of the questionnaire are provided in Table 1.

**Table 1 T1:** Contents of Health Care Practitioner Questionnaire

Domain	Outcome Measures	Study Phase
**Clinical experience**	Length of time qualified	1
	Post-graduate training	1,2,3
**Self-confidence**	Self-confidence in managing back pain patients [35]	1,2,3
**Beliefs and attitudes**	Pain Attitudes and Beliefs Scale (PABS) [33,34]	1,2,3
**Reported clinical behaviour**	Clinical case vignettes of patients with non-specific low back pain with items relating to investigations, referrals, advice and medication	1,2,3
	Changes in management of low back pain following best practice updates/training programme	2,3
**Education**	Future learning needs	2,3

Care processes and actual clinical behaviour: We will collect data on health care practitioners' actual clinical behaviour from anonymised GP medical record reviews and physiotherapy case report forms, for patients who consent to the study team accessing their medical records. We aim to collect data on primary care consultations, ordering of diagnostic tests (radiographs, MRI and CT scans), prescribed medications, referrals to other professionals or services and issuing of sickness certificates. Additional data from physiotherapy case report forms will include the physiotherapist's view of the patient's key problems and targets for treatment, the treatment approaches used, the advice given and the number and length of treatment sessions.

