### The sub-grouping tools and targeted treatment approaches

Two versions of a previously developed and validated subgrouping tool for use in primary care [19] will be used. The tools include key physical and psychological predictors of outcome in LBP. A 6-item computer-based subgrouping tool will be embedded in the EMIS GP computer system, for use in real-time GP/patient consultations. Following completion, patients are categorised as either at low (a score of 2 or less) or high (a score of 3 or more) risk of poor outcome and a recommendation is made about whether or not a referral to physiotherapy is likely to be most appropriate. Patients classified as at low risk of poor outcome are recommended to receive best primary care advice and management by the GP, to include a screen for red flags, reassurance about their good prognosis, the benign nature of their pain, and simple messages and advice about pain relief, appropriate physical activity levels, return to normal activity (including work), avoiding bed rest, appropriate use of pain relieving modalities and the role of further investigations. To reinforce these key messages, a brief information sheet will be given. No onward referral to other services is recommended although patients will be advised to re-consult if symptoms persist. Patients at high risk of poor outcome are recommended to be referred to physiotherapy. The GP and patient are then able to use this recommendation in their decision-making.

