#### Patients

Scoping work in preparation for this study has provided us with information on rates of consultation and current referral pathways, by which we can assess the expected recruitment and determine the power we will have to detect clinically important changes in patient outcome. The consultation rate for back pain in local general practices ranges from 6-10% annually. We aim to invite 7 GP practices (population of approx 45,000 adults aged 18 years or over) from which we expect at least 2,700 LBP consulters per year. Previous research suggests that approximately 50% of patients will be willing to consent to completing the questionnaires [45]. Based on these figures, we anticipate that within the timeline of the study (across both phases 1 and 3), recruitment of 1000 patients should be feasible.

A difference of 2.5 points in RMDQ [37] change scores is considered to be a minimum clinically important difference [46]. We wish to test the superiority of the subgrouping for targeted treatment system (phase 3) over usual primary care (phase 1) in relation to this 2.5 point difference for those patients in the high and medium risk subgroups, and to test for non-inferiority of the new care system compared to usual care in the low risk subgroup. A weighted sample size (based on the timeline ratio of 1:2 (phase 1: phase 3) of 50 patients (phase 1) and 100 patients (phase 3) is powered at about 80% to detect a 2.5 point difference, assuming a standard deviation of 5 and using a 5% two-tailed significance level. Based on our pilot work, we expect 20% of back pain patients to be classified as at "high-risk" of poor outcome, 40% to be at "medium-risk" and 40% at "low-risk". Thus, our expected study size of 1000 patients will enable us to evaluate this clinical difference across the three risk subgroups, and has 80% power to detect a 'small' effect size of about 0.2, equivalent to a mean difference in RMDQ scores of approximately 1, over the total study population (taking into account 20% loss to follow up).

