### Data analysis

#### Health care practitioners' attitudes and behaviour and care processes

A descriptive summary of the characteristics of the participating GPs and physiotherapists will be provided. To assess differences in health care practitioners' attitudes between phase 1 and phase 3, we will compare baseline mean scores and follow-up mean scores for the self-confidence and PABs scales using matched-analyses techniques (e.g. paired t-test) based on before (phase 1) and after (phase 3) matching of scores to individual health care practitioners. The matched-analyses are based on evaluating the same health care practitioners before and after; a sensitivity analysis using unmatched approaches (e.g. unpaired t-test) will be used if the pool of practitioners in phase 3 is not exactly the same as that in phase 1. As well as providing the best estimate of the true mean difference, we will also present 95% confidence interval estimates for the difference and give p-values for the statistical tests performed. Mean changes in attitudes scores (3 questionnaires: before the quality improvement interventions, immediately after the quality improvement interventions and 12 months after the quality improvement interventions) will also be described.

Behaviour measures, relating to the two case vignettes, follow categorical or textual response formats and differences over time will be described. Health care practitioner behaviour differences between time points will also be statistically evaluated by comparing data of their actual clinical practice, e.g. health care consultations, medication prescriptions, sickness certification and patterns of referral obtained from medical record downloads for patients who consent to record reviews and from physiotherapists' case report forms. Furthermore, GP responses to the computer "pop-up" prompt on 'chronicity risk' (low; medium; high) and presence of 'yellow flags' (no; yes) will be compared to patient questionnaire responses to the subgrouping tool; the percentage agreements would be expected to be higher after the quality improvement intervention. These analyses, based on patient measures, are unmatched and will follow between-group techniques i.e. unpaired t-test, chi square test and regression methods (as described below for clinical outcomes).

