#### Clinical outcomes for patients

The primary outcome measures of patient benefit will be back pain-related disability (measured on the RMDQ [37] and pain catastrophising (measured on the catastrophising subscale of the Coping Strategies questionnaire [38] at 6 month follow up. Primary analysis of the patient data will follow the principles of "intention to treat", to compare outcomes of patients in phase 1 (pre-intervention) to those of patients in phase 3 (post-intervention). A "per-protocol" analysis, based on the evaluation of phase 3 patients who were treated with strict adherence to the subgrouping tool allocation rule (versus all phase 1 patients) will be carried out as a secondary comparison. Estimates of treatment effects, i.e. comparative outcomes for phase 1 (pre-intervention) versus phase 3 (post-intervention), with 95% confidence intervals will be calculated using linear regression (for numerical outcomes) and logistic regression (for categorical outcomes). Analyses will be carried out both unadjusted and adjusted for baseline imbalances in certain variables i.e. age, gender and baseline values of key outcomes. Statistical adjustment is necessary as this is an observational, before and after study design, and thus open to the possibility of confounding bias; adjustment will ensure parity of key baseline patient characteristics across phases 1 and 3. Analyses will be carried out at each patient follow up time point (2 and 6 months) for primary and secondary outcome measures; the primary endpoint is 6 months. Analyses will be performed on available data, and on imputed datasets based on the method of multiple imputation [47]. We will use STATA and SPSS for the analyses.

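### GP referral is compared between phases without a risk-group term, so the stated analysis cannot show whether referral became matched to risk or merely rose or fell for everyone

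*Protocol article*

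**What the plan says.** Objective (ii) under Study Aims is to "change GPs' and physiotherapists' LBP-related attitudes and clinical behaviours using the subgrouping for targeted treatment approach". For GPs, the section on the sub-grouping tools gives that approach two directions. For low-risk patients, "No onward referral to other services is recommended although patients will be advised to re-consult if symptoms persist". For the rest, "Patients at high risk of poor outcome are recommended to be referred to physiotherapy"; the GP version of the tool has only two categories, and the Phase 2 section makes clear that both medium and high risk are meant for physiotherapy referral.

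The Phase 1 section on care processes lists what is taken from the records of consenting patients: consultations, and "ordering of diagnostic tests (radiographs, MRI and CT scans), prescribed medications, referrals to other professionals or services and issuing of sickness certificates".

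The Data analysis section on practitioners then says: "Health care practitioner behaviour differences between time points will also be statistically evaluated by comparing data of their actual clinical practice". Referral patterns are among the examples given. On method: "These analyses, based on patient measures, are unmatched and will follow between-group techniques i.e. unpaired t-test, chi square test and regression methods", the regression being the one described for clinical outcomes. That regression is unadjusted, or adjusted for age, gender and baseline values of the main outcomes. Risk group is not in the list. The risk-specific hypotheses under Sample Size concern the RMDQ only.

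**The concern.** Changing behaviour by means of the tool means, for a GP, referring fewer low-risk patients and more of the others. The comparison described is by phase alone. Read as a pooled comparison, it estimates a weighted sum of two changes that the system intends to have opposite signs.

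This has two consequences. First, the result does not identify the change that objective (ii) is about: referring more of everyone and referring according to risk can give the same answer. Second, where the two changes offset, the test has little power although practice has moved in both groups. The impact on GP behaviour and on the process of care are key secondary objectives in the Abstract, so a misleading answer here matters.

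**Working it through.** **Inputs from the protocol.** Risk mix 40% low, 40% medium, 20% high; 1000 patients; phase ratio 1:2; two-sided 5% (all Sample Size, Patients). This gives 333 v 667 overall, 133 v 267 at low risk and 200 v 400 at medium/high risk.

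**Assumption.** The protocol gives no phase 1 referral rate. I take 30% in every risk group for illustration and vary it in step 3.

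**The plan's own power figure.** The only one is for the RMDQ. With 50 v 100 patients, a 2.5-point difference and SD 5, the normal approximation gives 82%, in line with the stated figure of about 80%. No power is stated for referral.

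**Formulae.** Pooled change = 0.4 × (change at low risk) + 0.6 × (change at medium/high risk). Standard error of a difference in proportions = √[p₁(1−p₁)/n₁ + p₃(1−p₃)/n₃]. Phase-by-risk contrast = (change at medium/high) − (change at low), with standard error √(SE_low² + SE_MH²). Power = Φ(|difference|/SE − 1.96), plus a negligible lower tail except near zero difference, where it equals the 5% level.

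**Step 1: can the pooled test recognise targeting?**

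| Phase 3 scenario (phase 1 = 30%) | Overall rate | Pooled z | Pooled power | Contrast | Contrast power |
|---|---|---|---|---|---|
| Uniform: 40% in both groups | 40% | 0.10/0.0315 = 3.18 | 89% | 0 | 5% |
| Targeted: low 20%, medium/high 53.3% | 0.4×20 + 0.6×53.3 = 40% | 3.18 | 89% | 33.3 points, SE 6.2, z 5.37 | over 99% |

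The pooled test is identical in the two rows; the contrast separates them.

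**Step 2: power when the shifts offset (phase 1 = 30%).**

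| Shift, low / medium-high | Net change | Pooled power | Contrast power |
|---|---|---|---|
| −15 / +10 | −6 + 6 = 0 | 5% | 98% |
| −20 / +15 | −8 + 9 = +1 | 6% | over 99% |
| −10 / +10 | −4 + 6 = +2 | 10% | 90% |

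With 800 patients in place of 1000, the first row becomes 5% v 96%. These rows describe partial and uneven uptake. In the first, low-risk referral moves 15 of the 30 points to the recommendation (50%), and medium/high moves 10 of 70 (14%).

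**Step 3: full uptake.** If every low-risk patient stays with the GP and all others are referred, the overall rate is 0.4×0 + 0.6×1 = 60%. Pooled power against a phase 1 rate of 30% or 40% is over 99%; 45%: 99.5%; 50%: 85%; 55%: 33%; 60%: 5%; 65%: 33%; 70%: 88%. It falls below 80% only for phase 1 rates of about 51-69% (50-70% with 800 patients, 47-72% with 500).

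**The case against.** **Cancellation is not the general case.** A reader might infer that full uptake of the tool would test as no change. The documents do not support that. From 30% referral, full uptake doubles the overall rate and the pooled test would almost surely detect it. Even equal partial uptake in both groups gives pooled power of 82% at 30% uptake, 97% at 40% and 99.7% at 50%. The Phase 2 section also provides for a possible rise in physiotherapy demand. This stands: masking needs either a phase 1 rate near 60% or uptake that is much stronger at low risk.

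**The text does not spell out a pooled rate.** It speaks of referral patterns in patients who consent to record review, and a risk split could sit in an analysis plan that is not shown. It stands that the pooled reading is an inference. But the article does state the comparison (between time points), the techniques and the adjustment variables, and none of these carries risk group.

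**Other measures of uptake exist.** The GP's risk rating is compared with the patient's own tool answers, and agreement is expected to be higher after the intervention. That covers recognition of risk in both phases, but not whether referral followed risk. The per-protocol set, "phase 3 patients who were treated with strict adherence to the subgrouping tool allocation rule (versus all phase 1 patients", uses adherence, but defines it for phase 3 only. Vignettes, audit of tool use and interviews add context; none is a before-and-after measure of risk-matched actual referral. Nor does the plan contain a rule by which one referral test decides whether behaviour changed, so it cannot be said that GPs would necessarily be misreported.

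**Conclusion.** The point holds in a limited form. As described, the phase comparison of referral has no risk-group term and so cannot show whether referral became matched to risk. This does not depend on a particular phase 1 rate; at an assumed 30%, indiscriminate and targeted change both give 89% pooled power, against 5% and over 99% for the phase-by-risk contrast. Loss of power through offsetting is a conditional second risk: for full uptake it arises only at phase 1 rates of about 51-69%, and at lower rates only with partial uptake that is stronger in low-risk patients. The figures rest on the protocol's 40/60 mix, 1:2 ratio and 1000 patients, and on referral rates that I have assumed. A change is advisable because the objective is a key secondary one and the data are already being collected.

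**What to change.** In the Data analysis section on practitioners' behaviour, analyse physiotherapy referral by logistic regression on phase, risk group and their interaction, with the covariates already listed for clinical outcomes. Define risk group as low v medium/high from the tool answers in the patient questionnaire, scored by the same rule in both phases. Report the phase difference in referral separately for low and for medium/high risk, in percentage points as well as odds ratios, since the calculations above are on the difference scale. Base any statement about targeted referral on the interaction, and keep the overall referral rate as a measure of workload.

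This changes the analysis wording only and needs no new data. There are two costs. Intervals within a risk group are wider: in the −15/+10 example the standard error is about 4.5 points at low risk against 3.1 for the overall rate. And the questionnaire is posted after the consultation, so risk group is measured after the GP's advice and referral decision and, in phase 3, after contact with the new system. That should be stated as a limitation.
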